# LIST OF ABBREVIATIONS

| AT | Adipose tissue |
| --- | --- |
| SAT | Subcutaneous adipose tissue |
| VAT | Visceral adipose tissue |
| MRI | Magnetic resonance imaging |
| RMR | Resting metabolic rate |
| PA | Physical activity |
| WC | Waist circumference |
| TG | Triglyceride |

# PROTOCOL SUMMARY

| **Title:** | **Differential effect of weight-loss diet strategies on dynamics of abdominal and other fat depots and metabolic risk – the CENTRAL study: intervention trial** |
| --- | --- |
| **Précis:** | **Methods**: an estimate of 250 participants who have either a. central obesity or b. lean participants with poor dietary habits combined with hyper TG will be randomized by median VAT to the following groups: **Group 1:** low-fat diet. **Group 2 :** Low-carb /Mediterranean high MUFA and PUFA diet diet. Specific food items will be provided. After 6 months of intervention, the diet groups 1 and 2 will be re-randomized to continue with diet only or with combination of 4 hours/week aerobic and resistance gym exercise for the subsequent year, divided by 4 equal size groups of **Group A** (low-fat diet only), **Group A+** (low-fat diet +physical activity) , **Group B** (Low-carb/ high MUFA & PUFA diet only) and **Group B+** (Low-carb/ high MUFA & PUFA diet + physical activity). All groups will be guided for their dietary intervention by nutritional sessions. All the participants will be followed by 1.5-Tesla MRI imaging of fat and muscle, blood and urine biomarkers, clinical measurements (weight, waist circumference, blood pressure, energy expenditure) and electronic questionnaire of dietary, lifestyle and medical information. Furthermore, genetic tests will be performed following a genetic ethical committee approval. |
| **Objectives:** | To assess whether distinct lifestyle strategies can differentially affect specific body adipose pools.  ***Objective 1:***  To compare the effects of: low-carb/high-MUFA; and the currently recommended diet by the American Heart Association (low-fat diet) on the dynamics of body fat compesition (mainly VAT) during weight loss and regain-plateau phases by MRI with and without physical activity. ***Objective 2:***  To assess the effect of Low-carb/MED and Low- fat diets with or without PA on the dynamics of abdominal suncotenius intra-hepatic fat among participants with abdominal obesity or dyslipidemia. |
| **Endpoint** | Primary Endpoint: Body fat composition (changes in VAT). Important Secondary Endpoints: changes in abdominal subcutaneous fat sub-depots and hepatic fat. |
| **Population:** | Healthy adults with abdominal obesity/dyslipidemia. |
| **Phase:** | Phase 3 |
| **Number of Sites enrolling participants:** | Nuclear Research Center-Negev, Dimona, Israel  250 participants |
| **Description of Study Agent :** | Lifestyle (a low-fat (LF) or Mediterranean/low-carbohydrate (MED/LC+28g walnuts/day) diet with/without added moderate physical activity) intervention |
| **Study Duration:** | 42 months |
| **Participant Duration:** | 18 months  *Time (in months) it will take for each individual participant to complete all participant visits* |

# SCHEMATIC OF STUDY DESIGN

**Flow chart of the CENTRAL study**

[figure not shown]

# 2 INTRODUCTION: BACKGROUND INFORMATION AND SCIENTIFIC RATIONALE

## 2.1 Background Information

**Introduction:**

*Abdominal obesity signifies fat distribution associated with increased risk for obesity-related co-morbidity*. Obesity – the conversion of chronic surplus in calories into excessive accumulation of adipose tissue – is becoming a major threat to human health in the twenty-first century^1^. The association between obesity and cardio-metabolic risk does not follow a simple linear relationship^2^; Whereas some individuals have largely increased body mass index (BMI) with minimal health consequence^3^, others display a complex of metabolic, endocrine and vascular abnormalities with even mild increase in BMI beyond the accepted upper limit of 25 kg/m^2^. The reasons for this variability in the toll of excessive adipose tissue accumulation on health are largely unknown. Yet, *the anatomical locations in which adipose tissue accumulates* may be a significant factor^4,5^; As noted decades ago, fat accumulation in the lower part of the body, also called gynoid obesity, is rather benign and may even be protective against obesity-related morbidity. In contrast, upper body fat accumulation, particularly in the abdominal region, strongly associates with increased risk for diabetes and cardiovascular disease.  *Abdominal fat consists of several distinct fat depots*. SAT, represents fat accumulation outside the abdominal cavity ^6^. Within the abdominal cavity fat accumulates mainly around the internal organs- VAT and in the omentum. Among moderately obese healthy men large inter individual differences are observed for total adipose tissue (AT) volume (6.9-59.3 liters), SAT (6.3-49.8 liters), and VAT (0.5-8.5 liters)^7^. VAT represented 18.3% of the total AT. A distinct retroperitoneal fat also exists. Multiple studies now demonstrate that different fat depots are in fact quite distinct in their metabolic and endocrine functions (^2,5^ and **Table 1**). Firstly, while the venous drainage of subcutaneous and retroperitoneal fat is to the systemic circulation, visceral and omental fat drain into the portal system, thus, communicating directly with the liver by virtue of secreted products. Yet in addition, gene array analyses demonstrate significant differences between the fat depots in multiple developmental genes, suggesting intrinsic, genetically-encoded heterogeneity between fat tissues ^8^. These translate into important functional differences, including relatively increased sensitivity of intra-abdominal fat to lipolytic stimuli, and differential secretion of various fat-derived "adipokines". Rodent models suggest that in response to chronic excess in calories, intra-abdominal fat mainly responds by hypertrophy (and large adipocytes are thought to be more insulin resistant and "dysfunctional"), whereas subcutaneous fat tends to respond by hyperplasia^9^. In established obesity the cellular composition of adipose tissue in different depots is also distinct, with macrophages infiltrating to a larger degree the intra-abdominal versus the SAT^10, 11^. *Intriguingly, although increased waist circumference correlates with increased intra-abdominal fat mass, it may in fact represent predominant expansion of different depots in the abdomen.* In fact, some individuals exhibit a predominant accumulation of abdominal subcutaneous or of intra-abdominal fat^11, 12^, potentially resulting in comparable waist circumference. The distinction between persons with "predominant intra-abdominal (IA) adiposity" versus those with "predominant subcutaneous (SC) adiposity" relies on determining the SC/IA ratio based on imaging approaches^11^, as will be described in Section c.2. Intriguingly, when measured, it is the intra-abdominal fat mass which best correlated with glucose intolerance, insulin resistance, low HDL, high TG and hypertension^13, 14^. *Visceral fat is therefore suggested as a unique, pathogenic fat depot^15, 16^*. Yet, a *causative role* for intra-abdominal fat in the co-morbidity of obesity is not well established, and is still debated.

**Table 1: Differences between VAT and SAT (Reviewed in^2, 5, 17^)**

| **Difference** | **SAT** | **VAT** |
| --- | --- | --- |
| *Anatomic:* Venous drainage  *Morphology:* Adipocyte cell size  *Cell composition:* infiltrating macrophages | Systemic  ++  + | Portal  +  ++ |
| *Metabolic:* Glucose uptake, synthesis and storage rate of triglycerides | + | ++ |
| *Endocrine:*  Insulin-stimulation of glucose uptake and signaling  Anti-lipolytic action of insulin, or alpha-2 adrenergic agonists  Lipolysis in response to beta-adrenergic stimuli  11-β-HSD expression | +  ++  +  + | ++  +  ++  ++ |
| *Adipokines and secreted products:*  Leptin  Adiponectin  IL-6, IL-8, PAI-1, angiotensinogen | ++  +  + | +  ++  +++ |
| *Proliferantion:*  Tendency to proliferate of pre-adipocytes  Expression of PPAR-gamma and response to TZD | ++  ++ | +  + |
| *Stress pathways:*  Expression of JNK, p38MAPK, IKK, ERK  Phosphorylation (activation) of JNK and p38MAPK | +  + | ++  +++ |

*There are several comparable dietary strategies to induce weight loss, but their effect on specific abdominal fat depots is unclear*. The effectiveness for weight loss^18-20^, and superiority for cardiovascular benefits^21^ of low-fat diets components is debated. Recently we completed a 2-years intensive workplace-based Dietary Intervention Randomized Controlled Trial (DIRECT)^22^ among 322 participants, who were assigned to three intervention arms - Low-fat diet, Mediterranean diet (MED), and low-carbohydrate (low-carb) diet. Adherence was 95% at 1 year and 85% at 2 years. The results [see details in the preliminary (c.3.) and figures sections] suggest that whereas the low-carb diet was superior in improving lipid profile and weight loss, the Med diet (high in mono-unsaturated fat-MUFA) provided the largest decrease in circulating insulin and glucose levels. All three arms induced similar dynamics in weight, revealing a weight-loss phase (0-6 months) and a subsequent regain-plateau (6-24 months) phase (N Engl J Med 2008). Specific loss of VAT mass has mostly been shown in response to exercise training^23^. Gene expression of adiponectin in VAT and SAT is modified by physical training^24^. However, dietary strategy to preferentially promote loss of VAT is unknown. Several lines of evidence suggest differential roles of macronutrients in the *accumulation* of intra-abdominal (visceral) adipose tissue. VAT cells have a two-fold higher glucose uptake rate and de-novo lipogenesis capacity compared with SAT cells^25^. Glucose-stimulated insulin secretion may also have preferential effects on VAT, as insulin-stimulated glucose uptake and lipogenesis, and the stimulation of the expression of 11-β-HSD1 with resulting increase in active cortisol, are more evident in VAT, enhancing VAT accumulation^26^. Feeding rats with a high sucrose diet increase not only muscle insulin resistance, but also VAT mass^27^, at least partly by promoting cell hypertrophy^28,29^. In a 4-week intervention study among 22 human obese subjects, a larger decrease in VAT measured by computed tomography was observed in the low-carbohydrate diet group compared to the high-carbohydrate diet group^30^. *It is therefore possible that reducing carbohydrate load may preferentially decrease VAT accumulation*. In contrast, dietary fat explained only two percent of the variance in general adiposity, and was unrelated to VAT mass when measured in cross-sectional studies^31^. A recent study on 42 monkeys compared diets containing either monounsaturated fatty acids or an equivalent diet containing trans-fats for 6 years^32^. It was shown that trans-fat-fed monkeys gained significantly more weight, associated with increased intra-abdominal fat deposition and insulin resistance, compared to monkeys fed diet rich in monounsaturated fatty acids. In humans, in a cross-sectional study among 334 female twins there was no relationship between total dietary fat composition and adiposity^33^. However, in women at low genetic risk of abdominal obesity, subjects with higher polyunsaturated fat intakes had about 50% less central abdominal fat than subjects with lowest intake. Thus, a suggested preventive strategy for VAT accumulation may include limiting dietary carbohydrates and apparently, increasing monounsaturated fats^34^. Therefore, some evidence suggests that VAT accumulation may be linked to carbohydrate load in the diet, whereas the fat load (accept for trans-fatty acids) plays a minor, or even protective role (in the case of monounsaturated fat). *However, large-scale intervention trials assessing whether limiting carbohydrates and increasing monounsaturated fat can assist in inducing VAT loss beyond the weight loss induced by conventional hypocaloric diet are required to establish the relationship between dietary macronutrients composition, intraabdominal adiposity and insulin resistance.*

## 2.2 Rationale

Although accumulation of intra-abdominal fat may be pathogenic, it is unknown whether different diets improve metabolic state through differential effects on intra-abdominal versus subcutaneous-abdominal adipose tissue. While inducing similar global weight loss, low-carbohydrate/Mediterranean (LC/MED) diet strategy more favorably affects "pathogenic" abdominal fat depots when compared to the conventional low-fat diet (LF). These nutritional strategies initiated on top of exercise may manifest by differences in the maximal extent and/or dynamics of decrease in the mass of abdominal fat depots, and correspond to improvement in metabolic risk markers. For this, we propose an 18-month dietary and exercise intervention randomized controlled trial (the CENTRAL study). We hypothesize that differential dynamics in various fat depots: as SAT and VAT in response to two opposing dietary strategies mediate the beneficial metabolic effects during weight loss and regain phases.

Significance – The results of the present study will enhance current understanding on the mechanistic role of different abdominal fat depots (mainly VAT) in the pathogenesis of obesity. Particularly, it will increase current resolution in linking *dynamic* alterations in abdominal fat depots with various components of obesity-related metabolic dys-regulation. From a nutritional point of view, it will unravel the potential differential effect of macronutrients (carbs versus fat) in driving central adiposity. As for public health, the results will shed light on effective, health-promoting lifestyle intervention strategies, and whether they can be tailored individually based on abdominal fat distribution at baseline. This would be achieved by means of addressing the major limitations of currently available studies in the literature, by utilizing long-term intervention study with an expected high adherence rates.

## 2.3 Potential Risks and Benefits

### 2.3.1 Known Potential Risks

• Discomfort during MRI and RMR procedures.
• Dedication of time to workshops, filling out questionnaires and various follow-up tests.
• Discomfort during the blood draw.
• To the best of our knowledge, no risk to participants is expected.

### 2.3.2 Known Potential Benefits

• Participation in nutrition workshops with clinical dietitians.

• Free gym membership (for half of the participants).
• Imaging of fat tissue in the body. A radiologist will review the findings of the anatomical scan and create contact if further investigation is required.
• Receiving a detailed personal report summarizing all their measurements after the completion of the trial.

# 3 OBJECTIVES AND PURPOSE

***Objective 1:***  To assess the effect of Low-carb/MED and Low- fat diets with or without PA on the dynamics of body fat compesition (mainly VAT) during weight loss and regain-plateau phases by 1.5-Tesla MRI.

***Objective 2:***  To assess the effect of Low-carb/MED and Low- fat diets with or without PA on the dynamics of abdominal suncotenius intra-hepatic fat among participants with abdominal obesity or dyslipidemia.

# 4 STUDY DESIGN AND ENDPOINTS

## 4.1 Description of the Study Design

**Experimental design and methods**

*Global approach and study population:* The proposed 18-month intervention study will commence in one phase in a large research center workplace, located in Dimona in the south of Israel. The suitability of this setting is proven in several studies characterized by tight follow-up and/or interventions, which we performed in recent years^22,36-37^. Its advantages include an integral medical center, the possibility to perform most procedures (intervention and follow-up) within the workplace, and a secluded set of cafeterias amenable to dietary intervention Randomization- After performance of baseline measurements, the enrolled participants will be entered sequentially onto a list of random group assignments without stratification.

**Intervention**: In this a randomized clinical trial, participants will be randomized first for two diet groups: A. Low-fat diet; B. Low carbohydrate/Mediterranean diet, with 28g a day walnut supply, rich in polyunsaturated fatty acids (PUFA). All groups will be counseled by a clinical dietitian in dietary sessions that will delivered at work, 90 minutes each, every week during the first month of intervention, and then every month for the remainder of the trial. Diets will be equal-caloric for the entire study period. **Group A** – Low fat diet based on American Heart Association guidelines, will be guided to consume 30% of calories from fat, 10% of calories from saturated fat, and an intake of up to 300 mg of cholesterol per day. **Group B** – Low-carb/Mediterranean (high PUFA) diet is based on a combination and optimization of the Low-carb and Mediterranean diets tested in the DIRECT trial. Participants will be required to consume up to 20–40g of carbohydrates per day for the 2-month induction phase and immediately after religious holidays, with a gradual increase to a maximum of 120g per day to maintain their weight loss. Additionally, 28 g of fresh walnuts will be provided from the second month of intervention (see Table 2 for more details).

The second randomization will be performed after six months of the dietary intervention. The dietary groups will be further divided into PA (A+, B+) and non-PA (A-, B-) groups. The participants assigned to PA groups will get 12 months free supervise gym membership. The PA intervention will be mostly aerobic exercise training (80%) and resistance training three times a week, for 30 minutes in the first month, 50 minutes in the second to fifth months, and 80 minutes for months six to twelfth. The PA participants will be guided first in the gym with the support of the professional sport trainers. We will follow the PA participants online by electronic gym card recording their frequency of access and duration to the sport center and will call them frequently to encourage adherence.

***Intervention:*  Arm A:** the 2006 currently recommended diet by the American Heart Association (AHA) ^35^ (Low-fat) calorie restricted diet, a more revised statement since the AHA 2000; **Arm B:** guidelines^40^Low-carb/MED non-calorie restricted diet (n=125). Based on our preliminary results, low-carb and Mediterranean diets each showed beneficial effects on several biomarkers. Thus, here we suggest to utilize an optimized diet strategy which combines the beneficial components of low carb (low-carb) and Mediterranean (high monounsaturated) diets (**Table 2**). For both arms moderate physical activity will be equally introduced and monitored. The participants will be guided to exercise 150 min/week of moderate intensity, primarily in the form of initiating walking. This will be monitored by podometers that will be provided. The advantage of this strategy is that the podometer reflects both exercise thermogenesis (walking) as well as components of Non-exercise activity thermogensis (NEAT)^41^. The format and quality of the sessions will be kept constant to ensure equal treatment intensity, except for the specific instructions and paper material distributed for each diet strategy.

*Strategies to promote and verify adherence^22^: i. Food color and nutrition data labeling:* Lunch is considered the main daily meal in Israel. As the self-serve cafeteria in the workplace is the exclusive source of lunch for the participants, we will label each food item and nutritional data for the entire cafeteria styles. After analyzing the recipes and raw foods using the Israeli nutritional database^42^, we will display in each food-label: calories, grams of carbohydrates, fat, and saturated fat per portion size. We will further color-code the food item labels by setting specific criteria to component contents of each diet. Each dish will be labeled with a full circle (= "feel free to consume") or half-circle (= "consume in moderation") according to the diet arm, using two different colors. *ii.* The entire intervention and most measurements will be performed in the workplace, continuously monitored by the nurse study. Furthermore, structured motivation telephone calls and ongoing messaging via the intranet communication system will be held by specifically-trained dietitians.

The participants will be required to fill in electronic questionnaires at baseline, 6, and 18 months, which include: i. a validated food frequency questionnaire (FFQ) ^43^ that includes 127 food items and 3 portion sizes pictures for 17-selected food items. The nutritional data will be analyzed in the Israeli nutrition database ^42^. ii. Physical activity questionnaire: transformation to metabolic equivalents ^39^. Medical information will be updated by the workplace medical center’s physicians. A uniquely-developed electronic interface for submitting the questionnaires will ensure the completeness of data by popping-up missing lines.^22^

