### 4.2.3 Exploratory Endpoints

# 5 STUDY ENROLLMENT AND WITHDRAWAL

## 5.1 Participant Inclusion Criteria

In order to be eligible to participate in this study, an individual must meet all of the following criteria:

• Either abdominal obesity [waist circumference >102cm (40 inches) for men and >88cm (35 inches) for women], or serum triglycerides (TG)>150mg/dL and high-density-lipoprotein cholesterol (HDL‑c) <40mg/dL for men and <50mg/dL for women.
• Provision of signed and dated informed consent form
• Stated willingness to comply with all study procedures and availability for the duration of the
study.

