## 10.4 Description of Statistical Methods

### 10.4.1 General Approach

Results will be presented as means ± SD unless otherwise stated. Analysis of variance with a covariance (ANCOVA) test will be used in order to assess adherence to the interventions (attendance of the group sessions) and differences in changes nutrient intakes between the diet strategies. General linear models will be used to compare the trajectories of body weight and WC across the four intervention groups. We will use multivariate two-way ANCOVA and compare type of diet and physical activity as fixed factors (2*2 factorial design) to test changes in specific fat depots, using mean of differences and 95% CIs for each intervention group over time. Optional interactions between diet and exercise will be assessed by the ANCOVA models. To assess the effect of the combination of diet and PA, general linear models will be used with LFPA– as the reference. All models will be adjusted for age, sex, baseline abdominal obesity and 18-month weight change. Changes in the various fat depots and deposits will be evaluated both as absolute and relative changes. The association between changes in abdominal fat and intra-hepatic fat, and changes in levels of blood biomarkers will be tested using multivariate linear regression models, adjusted for age, sex, weight change, intervention group and baseline abdominal fat status (for the abdominal fat models) or baseline intra-hepatic fat (for the hepatic model). Homeostasis-model-assessment-of insulin-resistance (HOMA-IR) will be calculated according to the following equation: insulin (U/ml)×fasting glucose(mmol/liter) ÷22.5. Statistical analysis will be performed with IBM SPSS (version 23). All *P*-values will be two-sided, and *P*<0.05 will be considered statistically significant.

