## 10.6 Measures to Minimize Bias

### 10.6.1 Enrollment/ Randomization/ Masking Procedures

Participants will be randomly assigned to one of two equal-caloric diets for the entire study period: a low-fat diet (n=125) or a Mediterranean/low-carbohydrate diet (n=125). After 6 months of dietary intervention, each diet group will be further randomized into added PA groups (LF^PA+^, MED/LC^PA+^) or no added PA groups (LF^PA–^, MED/LC^PA–^) for the last 12 months of intervention. The randomization will be performed with an allocation ratio of 1:1 to the two treatment groups, within strata of baseline VAT area for the first randomization, and of address of residence (to ensure similar geographical distance from the gym) in the second randomization (in blocks of two). Participants will be randomized after all had been recruited, in one phase, after their strata characteristics will be defined.

The participants, who will be randomized in the same time point, will be aware of the intervention to which they will be assigned (open-label). Study investigators will be blinded to the intervention group identities.

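### Randomisation is described both as unstratified and as stratified by VAT and residence, and the depot-change models name neither the strata nor the measured baseline depot: a modest, conservative loss

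*Protocol*

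**What the plan says.** **Randomisation.** Section 4.1 (Experimental design and methods) states that after baseline measurements "the enrolled participants will be entered sequentially onto a list of random group assignments without stratification". Section 10.6.1 describes a 1:1 allocation "within strata of baseline VAT area for the first randomization, and of address of residence" "in the second randomization (in blocks of two"). It adds that "Participants will be randomized after all had been recruited, in one phase, after their strata characteristics will be defined". The Protocol Summary says only that participants "will be randomized by median VAT to the following groups" and are re-randomised at six months. It mentions neither residence nor simultaneous allocation. The version table in the Appendix is blank, so nothing marks any of these statements as superseded.

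**Analysis.** Section 10.4.1 will "compare type of diet and physical activity as fixed factors (2*2 factorial design) to test changes in specific fat depots", and "All models will be adjusted for age, sex, baseline abdominal obesity and 18-month weight change". How baseline abdominal obesity is coded is not stated. The protocol's only definition of abdominal obesity is the eligibility criterion in section 5.1: "Either abdominal obesity [waist circumference >102cm (40 inches) for men and >88cm (35 inches) for women". For the biomarker association models, the same paragraph of 10.4.1 uses a different term for baseline abdominal fat and does name baseline intra-hepatic fat. The randomised comparison of hepatic-fat change has no such term.

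**The concern.** Two things need attention, and they are separate.

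First, a list filled sequentially with no stratification and a one-phase allocation within strata are different procedures. Whoever prepares the allocation, or later justifies the model, cannot tell from the protocol which one applies.

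Second, the primary endpoint is change in VAT, and change generally depends on the starting value. The covariate list for the depot models is stated as applying to all models, yet it omits measured baseline VAT, the VAT stratum and residence. Leaving out a prognostic baseline value gives up precision. Stratifying on a prognostic factor and then leaving it out of the model makes the reported standard error larger than the true one. What is at stake is interpretability of the design and some power, not the validity of a positive result.

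**Working it through.** **1. The randomisation texts side by side.**

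| Place | Stratified? | Timing |
|---|---|---|
| 4.1 | No | Sequential entry on a list |
| 10.6.1 | VAT area (first), residence (second) | All in one phase, after recruitment |
| Protocol Summary | Median VAT (first) | Not stated |

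Section 4.1 conflicts with both others on stratification and with 10.6.1 on timing. The blocks of two are attached to the second randomisation; whether they also apply to the first is unclear.

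**2. The plan's own figure.** Section 10.5 gives a detectable VAT difference of 3.57 cm², alpha 5%, power 80% and N = 250, but no SD, so 250 cannot be reproduced. Solving backwards for 125 v 125: SD = 3.57 / [(1.960 + 0.842) × √(2/125)] = 10.07 cm². Whether that SD is meant to be adjusted for baseline cannot be told, so the precision question has to be put as a ratio.

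**3. Upper bound on the gain.** Assume equal variances σ² at baseline and 18 months, with correlation ρ (not in the documents). The unadjusted change score has variance 2σ²(1 − ρ). After adjustment for baseline it is σ²(1 − ρ²). The ratio is (1 + ρ)/2.

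- ρ = 0.5: 0.75, so 250 × 0.75 ≈ 188 participants would do the work of 250
- ρ = 0.7: 0.85, about 213
- ρ = 0.9: 0.95, about 238

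This is an upper bound, because the planned model is not unadjusted.

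**4. Gain over a model that already has an obesity covariate.** A simulation under the null used N = 250, the first randomisation stratified at the VAT median in blocks of two, and 4,000 runs per scenario. It assumed a correlation of 0.7 between VAT and waist, and 70% of participants with abdominal obesity. Each model contained diet plus one covariate. VAT is in SD units.

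| ρ | Empirical SE, obesity covariate | Empirical SE, baseline VAT | Variance ratio | Reduction |
|---|---|---|---|---|
| 0.5 | 0.1170 | 0.1097 | (0.1097/0.1170)² = 0.879 | about 12% |
| 0.7 | 0.0951 | 0.0924 | (0.0924/0.0951)² = 0.944 | about 6% |
| 0.9 | 0.0555 | 0.0548 | (0.0548/0.0555)² = 0.975 | about 2.5% |

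These gains belong to VAT-stratified allocation. Under an unstratified list the gain would be somewhat larger, because allocation would not already balance part of the VAT difference.

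**5. Calibration of the standard error in the same simulation** (model SE ÷ empirical SE, with type I error at nominal 5%).

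| ρ | Obesity covariate | VAT stratum | Baseline VAT |
|---|---|---|---|
| 0.5 | 1.043 (4.0%) | 0.994 (4.8%) | 0.998 (4.7%) |
| 0.7 | 1.009 (4.5%) | 0.982 (5.0%) | 0.977 (5.4%) |
| 0.9 | 1.013 (4.4%) | 1.007 (4.4%) | 1.006 (4.5%) |

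Simulation error on these ratios is about 1%, so only the ρ = 0.5 overstatement stands clearly apart from none. With no covariate at all the ratios were 1.083, 1.031 and 1.023 (type I error 3.3%, 4.0%, 4.1%). Age, sex, weight change, the physical-activity factor, residence and dropout were not simulated.

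**The case against.** The best defence is that the planned model already carries baseline information. A baseline obesity term stands in for part of baseline VAT, and if VAT status was what the authors meant, the VAT stratum is largely covered and only residence is missing. Exact coding is commonly settled in an SAP, which is not at hand. This largely stands. It is why the loss is modest, and why the fair criticism is that the term is undefined. A reader might conclude from section 5.1 that the covariate is certainly a yes/no waist indicator, but the documents use that cut-off only for eligibility.

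A reader might also infer a much larger loss by taking the variance reduction as r², with r the correlation between baseline VAT and its change. For r of 0.3 to 0.6 that gives 9-36%, or 250/(1 − r²) = 275 to 391 equivalent participants. The arithmetic is right, but the comparator is a model with no baseline information, which is not the planned one. The upper end is also hard to support: with equal variances r² = (1 − ρ)/2, so r = 0.6 needs ρ = 1 − 2 × 0.36 = 0.28.

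The two harms should not be added together. Standard-error overstatement arises only if allocation is stratified by VAT; chance imbalance in VAT is mainly a worry if it is not. Residence matters to the analysis only if it predicts VAT change, and the documents give no evidence on that.

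None of this touches the contradiction between 4.1 and the other two places, or the absence of the measured baseline depot from the covariate list.

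**Conclusion.** The concern holds in a limited form. The contradiction on randomisation is plain and needs no assumption. The omission of the measured baseline depot and of both stratification factors from the stated covariate list is equally plain. Its size cannot be taken from the documents. On assumed correlations of 0.5 to 0.9, a VAT-waist correlation of 0.7 and 70% with abdominal obesity, using baseline VAT in place of a waist-type covariate cuts the variance of the diet effect by about 12% to 2.5%.

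If the VAT-stratified scheme is used, the planned standard error is about 1-4% too large and type I error about 4.0-4.5%. A reader might infer from a misstated standard error that false positives are inflated; the direction is the opposite, with intervals slightly too wide and tests slightly conservative. Confidence is high on the contradiction and the omission, and low on the exact size of the loss.

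**What to change.** 1. Reconcile section 4.1 with section 10.6.1 and the Protocol Summary so that one scheme stands. For each of the two randomisations, state the stratification factor, its cut-offs or categories, the block size and the timing.
2. In section 10.4.1, replace baseline abdominal obesity in the depot-change models with the continuous baseline value of the depot analysed: baseline VAT for VAT, baseline hepatic fat for hepatic fat.
3. Add the stratification factors actually used. Section 10.6.1 gives no number or boundaries for the residence strata, so these must be defined first.

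The cost is a few degrees of freedom (how many depends on the number of residence strata) and the work of defining those strata. No extra measurement is needed: under 10.6.1, VAT and residence must both be known before the randomisation that uses them, and baseline MRI already covers hepatic fat. The 18-month weight-change covariate in the same sentence is measured after randomisation; it is a separate matter that this change does not settle.
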